#### Secondary outcomes

Secondary outcomes will be assessed using validated self-report instruments and neuropsychological tasks. Change in score/performance from baseline (T0), to post treatment (T1) and follow up (T2) will be examined by looking at within and between group effect sizes and standard deviations. These data will inform outcome measure selection for a future large-scale RCT.

### Outcome measures

See Table 1 for a summary of the measures collected at each timepoint.

**Table 1 T1:** Summary of outcome assessment by visit.

	**Screening**	**T0**	**During treatment**	**T1**	**T2**
Eating disorder diagnostic screen	X				
TDCS safety screen	X				
General health and lifestyle questionnaire	X				
Demographics		X			
Eating disorder examination questionnaire (EDE-Q)		X		X	X
Depression, anxiety, stress scale (DASS-21)		X		X	X
Food craving questionnaire—trait version		X		X	X
Clinical impairment assessment (CIA)		X		X	X
Difficulties in emotion regulation scale (DERS)		X		X	X
Barrett impulsiveness scale (BIS-11)		X		X	X
Visual probe task		X		X	X
Food attention network task		X		X	X
N-back task		X		X	
Wisconsin card sorting task		X		X	
Delay discounting task		X		X	
Affective go/no go task		X		X	
VAS measures		X	X	X	X
Assessment of tDCS discomfort/Side effects			X		
Semi-structured interview about treatment (optional)					X

#### Questionnaires measures

Participants will complete a battery of questionnaire measures at each assessment (T0, T1 and T2). These will assess ED psychopathology [Eating Disorder Examination Questionnaire (48)], general psychopathology [Depression, Anxiety and Stress Scale – 21 item version (49)], craving for food [Food Craving Questionnaire – trait version (50)], ED related clinical impairment [Clinical Impairment Assessment (51)], emotion regulation [Difficulties with Emotion Regulation Scale – 16 item version (52)], and impulsivity [Barratt Impulsiveness Scale (53)]. Self-reported weight and height will be used to calculate BMI.

#### Task measures of neurocognition

*Attention bias toward high calorie foods* will be assessed using the visual probe task described in Mercado et al. (54). In TANDEM, as participants will be taking part from home, webcam based eye-tracking technology (as opposed to specialist lab-based eye-tracking equipment) will be used to record eye movements.

*Food-related attention* will be assessed using the food-specific attention network task described in Heve, Stingl et al. (55) and in Mercado et al. (54). This task examines three components of attention (alerting, orienting, and executive function) using food (low- and high-calorie) and non-food picture stimuli.

*Working memory* will be assessed using the n-back task described in Meiron and Lavirdor (56). Accuracy (% correct responses) and reaction time for correct responses (ms) will be reported.

*Affective inhibitory control* will be assessed using the Face Affective Go/No Go task from the EMOTICOM neuropsychological test battery (57). Error rate and latency will be used to estimate inhibitory control, and reaction times will be used to calculate affective bias scores.

*Cognitive flexibility* will be assessed using the Wisconsin Card Sorting Test (58). Difficulties with set-shifting will be reflected in perseverative errors, thus, higher scores on this test indicate poorer performance.

*Preference for immediate vs. delayed rewards* will be assessed using the delay discounting task described by Kirby and Maraković (59). Modeling techniques are used to fit participant responses to the function that relates time to discounting. This produces a temporal discounting curve. The rate at which delayed rewards are discounted will be derived by calculating the area under the curve, and steeper discounting will be reflected by a smaller area under the curve (60).

#### Optional semi-structured interview

All participants (i.e., including those who received ABMT only) will be invited to complete a semi-structured interview about the treatment experience. This interview, developed for the TANDEM trial, was based on previous semi-structured interviews about tDCS treatment by Gordon et al. (33) and Smits et al. (61). Questions examined seven domains of acceptability: affective attitudes, burden, ethicality, intervention coherence, opportunity costs, perceived effectiveness, and self-efficacy. Interview prompts are included in the Supplementary material.

#### Within session measures

At each treatment session, participants will complete measures of current symptoms and, where relevant, tDCS related discomfort. Before each treatment begins, participants will complete an online “check in” questionnaire which asks about episodes of binge eating since their previous session and, where relevant, adverse events/side effects that may be related to tDCS. They then complete 10-point visual analog scales (VAS) assessing current hunger, feeling of fullness, craving for food, urge to binge, level of tension, level of stress, level of discomfort, and feeling of low mood. At the end of each session, participants complete a “check-out” questionnaire which repeats VAS measures and, where relevant, asks about tDCS related discomfort during the session.

### Data analysis

The primary analysis will use the number of episodes of binge eating in a Poisson regression model with baseline adjustment. Descriptive statistics will be used to assess recruitment and retention rates, intervention adherence, and the quality and completeness of the data. In secondary analyses, a mixed model approach will be used to analyse the effect of treatment on primary (PO) and secondary outcomes (SOs), with baseline adjustment. To examine the whether the effect of treatment is different for different levels of overweight or obesity, BMI will be included in the model as an interaction effect. Effect sizes will be analyzed and reported for PO and SOs. For the Poisson regression, rate ratios will be reported. For binary outcomes, odds ratios will be reported. For quantitative outcomes, standardized differences will be reported. Primary parameters will be time vs. treatment interactions at both timepoints after baseline. *P*-values will be reported but for exploratory purposes only (i.e., they will not be interpreted to accept or reject the null hypothesis). The analyses will be done in the intent to treat population, which is defined by including all patients with baseline assessment. Outcome data already obtained for participants who discontinue or deviate from the intervention protocol will be kept and analyzed. Analyses will be conducted using RStudio (62).

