## Study aims

The primary aim of the TANDEM trial is to assess the feasibility of using 10 sessions of concurrent food-specific ABMT (henceforth, ABMT) and self-administered right-dlPFC anodal tDCS as a treatment for BED. This intervention will be compared to training in combination with sham stimulation, stand-alone training, and a “no treatment” waiting control condition. In doing so, we aim to acquire key information to inform the design of a large-scale RCT.

Specifically, we aim to:
estimate the rate ratio for the proposed primary outcome, change in the number of monthly episodes of binge eating from baseline to follow up. This will inform the sample size calculation for a large-scale RCT.explore the feasibility of conducting a large-scale RCT of at-home self-administered concurrent tDCS and ABMT in adults with BED by assessing recruitment, attendance, and retention rates;assess acceptability by examining participant ratings of treatment acceptability and tolerance, and by evaluating feedback provided during semi-structured interviews;determine the best instruments for measuring primary and secondary outcomes in a full trial by examining the quality, completeness, and variability in the data.

The primary clinical endpoint will be the change in monthly episodes of binge eating from baseline to follow-up. Secondary aims will focus on evaluating changes in overall ED pathology and general psychopathology, changes in attention bias toward high-calorie foods, and changes in executive functioning from baseline to 6-weeks post treatment completion.

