### Sample size

As TANDEM aims to establish feasibility rather than between-group differences, an a priori sample size calculation is not necessary. Guidance suggests that, where available, sample size should be based on previous feasibility or pilot studies of a similar intervention, or with a similar primary outcome measure or trial design. Where this information is lacking, it is argued that a total sample between *n* = 12 and *n* = 50 is sufficient for robust assessment of feasibility outcomes (39). Previous comparable trials in BED included 20 participants in each trial arm [e.g., (31, 41)]. As this trial includes four arms, we have chosen a target end study sample size of *n* = 80. Assuming the attrition to follow-up rate is ~10% [as found in previous recent BED treatment trials, e.g., (42)], we will recruit an actual sample size of 88 (22 participants/group).

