### Outcome assessment

#### Primary outcomes

The primary clinical outcome will be monthly episodes of binge eating, as measured by the Eating Disorders Examination Questionnaire [EDE-Q; i.e., change in the number of monthly episodes of binge eating from baseline (T0) to follow-up (T2)]. Medians and rate ratios (with confidence intervals) will be reported, and these will inform the minimum sample size required for a fully powered large-scale RCT. Rates for recruitment and retention to 8-week follow up will also be reported to provide insight into the time and resources needed for a larger trial.

Intervention acceptability will be assessed in two ways. First, by asking participants the following two questions at post treatment (T1) and follow-up (T2) assessments: (1) “If you could continue with this treatment, would you?” (Yes/No) and “Would you recommend this treatment to a friend who was struggling with binge eating?” (Yes/No). The intervention will be viewed as acceptable if at least 75% of those who receive the real concurrent treatment indicate that they would continue the intervention if given the opportunity and/or if 75% would recommend the treatment to a friend. Second, at or near-to the final (T2) assessment, participants will be invited to complete an optional semi-structured interview about the treatment experience. This will provide qualitative data which will give insight into (a) whether participants viewed the treatment as acceptable and (b) why/why not. Interviews will be recorded, transcribed, and analyzed using thematic analysis.

Feasibility will also be assessed by looking at participant ratings of tDCS tolerability. Participants who receive tDCS will complete a 10-point visual analog scale (VAS) of tDCS discomfort after each session. We will then take the average of ratings across the ten sessions for each participant and use this to assess the average rating for tDCS related discomfort for the real tDCS + ABMT group. The intervention will be considered well-tolerated if this number is ≤4 (i.e., mild discomfort). Prior to beginning each tDCS session, participants will also report any side effects they have experienced since their previous session. The type and frequency of side effects will be reported for consideration.

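### The primary Poisson model makes no allowance for overdispersion, so intervals meant to inform the next trial's size will be too narrow to the extent that residual variance exceeds the mean

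*Protocol article*

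**What the plan says.** The outcome is a self-reported count per person. Primary outcomes: "The primary clinical outcome will be monthly episodes of binge eating, as measured by the Eating Disorders Examination Questionnaire", with interest in the change from baseline (T0) to follow-up (T2).

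The Data analysis section fixes the model: "The primary analysis will use the number of episodes of binge eating in a Poisson regression model with baseline adjustment". It adds the effect measure: "For the Poisson regression, rate ratios will be reported". A mixed model for the primary and secondary outcomes appears only among the secondary analyses, with no distribution given. P-values are declared exploratory.

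Two places give the output a planning role. The first specific objective under Study aims is to estimate the rate ratio for this outcome, and continues: "This will inform the sample size calculation for a large-scale RCT". Primary outcomes says: "Medians and rate ratios (with confidence intervals) will be reported, and these will inform the minimum sample size required".

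None of these sections mentions variance in excess of the mean. The article gives no mean, standard deviation or variance for binge counts.

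**The concern.** A Poisson model with its own standard errors is right only if people with the same baseline count and the same allocation share one expected count at follow-up. If their true rates have coefficient of variation CV around a mean m, the variance-to-mean ratio is φ = 1 + m × CV², which exceeds 1 whenever CV exceeds 0.

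The article suggests residual differences of that kind. The Introduction says that only about half of those completing psychological treatment or self-help report a substantial reduction or abstinence. Concomitant care allows other eating-disorder treatment during the trial. The inclusion criteria set no upper limit on episode frequency. Baseline adjustment removes part of this variation, but not differences in response or in parallel treatment.

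At stake is the trial's first listed objective. Because p-values are not to be interpreted, the interval carries the statement of uncertainty, and a model-based Poisson interval would claim more precision than the data hold. A fit that takes dispersion as 1 also does not estimate the dispersion, which whoever sizes the large RCT will need.

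**Working it through.** **The plan's own figure.** The article states no interval width, dispersion, power or alpha for the rate ratio. Its only sample-size figure is for recruitment: 80 completers (20 in each of four arms), about 10% attrition, 88 recruited. 80 × 1.10 = 88, while 80 / 0.90 = 88.9, or 89. The 88 reproduces to within one participant, so 20 per arm is used below.

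**Assumed inputs, not in the article.** Mean of 8 episodes per month at follow-up; φ from 1 (no overdispersion) to 10. For the next-trial illustration: rate ratio 0.7, comparator mean 8, 80% power, two-sided 5%.

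**Formulas, two arms of n = 20.**
- Poisson standard error of the log rate ratio: √(2 / (n × m)) = √(2 / 160) = 0.112.
- Actual standard error: √φ × 0.112. At φ = 5 this is 0.250.
- Interval: rate ratio multiplied or divided by exp(1.96 × SE). Poisson: exp(0.219) = 1.245. At φ = 5: exp(0.490) = 1.63.
- Actual coverage of the nominal 95% Poisson interval: 2Φ(1.96 / √φ) − 1, where Φ is the normal distribution function. At φ = 3: 1.96 / 1.732 = 1.132, giving 74%.
- Next trial, per arm: (1.960 + 0.842)² × φ × (1/8 + 1/5.6) / (ln 0.7)² = 7.85 × 0.3036 × φ / 0.1272 = 18.7 × φ.

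| φ | Coverage of nominal 95% Poisson interval | Widening needed (log scale) | Correct interval factor at mean 8 | Next trial, n per arm |
|---|---|---|---|---|
| 1 | 95% | 1.00 | 1.245 | 19 |
| 2 | 83% | 1.41 | 1.36 | 38 |
| 3 | 74% | 1.73 | 1.46 | 57 |
| 5 | 62% | 2.24 | 1.63 | 94 |
| 10 | 46% | 3.16 | 2.00 | 188 |

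Coverage and widening do not depend on the assumed mean. The last two columns do.

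**What φ = 3 looks like.** If half the participants have a true rate of 4 and half a rate of 12, the mean is 8, the between-person variance 16 and the Poisson variance 8. The total is 24, and 24 / 8 = 3. This illustrates scale only and is not an estimate.

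**Simulation with baseline adjustment.** Poisson regression of the follow-up count on arm and log baseline count was run with 20 against 20, 1,000 runs per setting, no treatment effect, and residual gamma variation between people. The nominal 95% Poisson interval covered 96% with no residual variation (estimated φ about 1.0), 83% at φ about 1.7, 70% at 2.7, 57% at 4.4 and 46% at 7.6. The loss therefore remains after baseline adjustment, and coverage is somewhat below what the formula gives at the same φ. Scaling the standard errors by the estimated dispersion, with 1.96 as critical value, gave 94% with no residual variation and 89–92% otherwise. That is most of the repair, and the reason for a small-sample correction.

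**The case against.** The strongest reply is that the article names a model family and an effect measure, not a variance estimator. Poisson regression with robust or scaled standard errors is still Poisson regression, and that detail may sit in a statistical analysis plan that is not shown. This stands as a limit on the claim: the article does not prove that dispersion will be held at 1. It does not remove the point, because an analyst following the text as written would fit an ordinary Poisson model.

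A second reply is that a person-level random effect in a count model would absorb between-person variation, and a mixed model is planned. That model is secondary and its distribution is unstated, so it does not repair the primary analysis.

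A third is that this is a feasibility study in which nothing is tested. That lowers the severity, but the interval still has a stated planning use.

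Several stronger readings are tempting and unsupported:
- A reader might infer that the intervals are certain to be far too narrow. Without any mean or variance in the article, the loss could run from none at φ = 1 to severe at φ of 3 or more.
- A reader might take the reporting of medians as an admission of overdispersion. Poisson counts are themselves right-skewed, so medians say nothing about variance against mean.
- A reader might infer that the large RCT will be sized on Poisson variance. No section says so, and Study aims includes examining variability in the data, so dispersion could still reach the planners.

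**Conclusion.** The point holds in conditional form. The article fixes a Poisson primary analysis for person-level binge counts, makes no allowance for extra-Poisson variation, and sends the rate ratios and intervals into planning. The rate-ratio estimate itself is not biased by this. The interval is too narrow by the factor √φ on the log scale, and a sample size computed under Poisson variance would be too small by about φ.

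The size depends on an unknown φ after baseline adjustment. Undercoverage is already material at φ = 2 (83%) and reaches 62% at φ = 5. That φ exceeds 1 is a judgement about this kind of outcome, supported only indirectly by the article. The interval factors and per-arm numbers rest further on the assumed mean of 8 and rate ratio of 0.7. This should be fixed, but it is not critical, since the trial is a feasibility study and its p-values are exploratory.

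**What to change.** State the primary model as negative binomial, or as Poisson with an estimated dispersion or robust standard errors, with a small-sample correction for arms of about 20. Keep the baseline adjustment. Report the estimated dispersion beside each rate ratio and interval, and say that this dispersion will be used when the large RCT is sized. If the full protocol or analysis plan already specifies such a variance, one sentence saying so is enough.

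The cost is a few lines of analysis text. No new data or participants are needed, which matters because recruitment has ended. The downside is wider, less favourable intervals and probably a larger next trial. The change should be fixed before the outcome data are analysed and reported as an amendment, as the Trial progress section already provides for.

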### Randomization

The study will use a randomized controlled design, stratified by age, gender and BMI. Participants will be randomly allocated to a study group in a 1:1:1:1 ratio. Randomization will be completed using the Sealed Envelope Simple+ randomization service (https://www.sealedenvelope.com/). After completing the T2 assessment, participants in the waiting control arm will be offered ABMT.

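### Age and gender, two of the three stratification factors, are in no stated model, and BMI enters only through a secondary interaction, so reported intervals will tend to be slightly wider than the design allows

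*Protocol article*

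**What the plan says.** The Randomization section of the protocol article says: "The study will use a randomized controlled design, stratified by age, gender and BMI". Allocation is equal across four arms: "Participants will be randomly allocated to a study group in a 1:1:1:1 ratio".

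The Data analysis section then describes two models.

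- Primary: "The primary analysis will use the number of episodes of binge eating in a Poisson regression model with baseline adjustment". No other covariate is named.
- Secondary: "In secondary analyses, a mixed model approach will be used to analyse the effect of treatment on primary (PO) and secondary outcomes (SOs"), again with adjustment for baseline.

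The next sentence introduces BMI. Its stated purpose is to examine "whether the effect of treatment is different for different levels of overweight or obesity", and to that end "BMI will be included in the model as an interaction effect". A few sentences later the section adds: "Primary parameters will be time vs. treatment interactions at both timepoints after baseline". On p-values it says that "they will not be interpreted to accept or reject the null hypothesis".

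Study aims and Primary outcomes state that the rate ratio for binge-eating episodes is to feed the sample-size calculation of a later, larger trial.

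**The concern.** Stratified randomisation reduces chance imbalance on the stratification factors, so the treatment estimate varies less from sample to sample if those factors are prognostic. A model that leaves them out does not see that reduction. It puts the variance they explain into the residual, and the intervals tend to be wider than the design allows. Here the analysis text names its adjustment explicitly, and that adjustment does not match the design: age and gender are absent from both models, and BMI is absent from the primary one.

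A narrower matter concerns the secondary mixed model. If the BMI interaction sits in the same model that supplies the treatment effect, that effect refers to a particular BMI and is not an overall effect. The section describes no separate model for the interaction.

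What is at stake is the quality of the estimates and intervals handed to the next trial. In a feasibility study that does not use p-values for decisions, these are the main statistical product.

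**Working it through.** **Inputs.** Sample size gives 20 completers in each of four arms (80), attrition of about 10%, and 88 to be recruited. The article gives no variance, event rate or prognostic strength, so these are assumed below.

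**The plan's own figure.** 80 × 1.10 = 88, and 80 / 0.90 = 88.9, that is 89. Conversely, 88 × 0.90 = 79.2. The stated 88 reproduces to within one participant, and 80 is used below.

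**Step 1: design against analysis.**

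| Factor | Stratified on | Primary Poisson model | Secondary mixed model |
|---|---|---|---|
| Age | yes | no | no |
| Gender | yes | no | no |
| BMI | yes | no | through an interaction with treatment |
| Baseline outcome | no | yes | yes |

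**Step 2: effect on the standard error (SE).** Let R² be the share of the variance remaining after baseline that the three factors explain. Then SE without / SE with = 1/√(1 − R²). To charge for three extra parameters, read R² as the observed share. The residual degrees of freedom are 80 − 5 = 75 (intercept, three arm terms, baseline) without the factors and 72 with them, so the net ratio is √[(1/(1 − R²)) × 72/75].

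| Assumed R² | Gross ratio | Net of 3 df |
|---|---|---|
| 0.02 | 1.010 | 0.990 |
| 0.05 | 1.026 | 1.005 |
| 0.10 | 1.054 | 1.033 |
| 0.20 | 1.118 | 1.095 |

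The net ratio breaks even at R² = 1 − 72/75 = 0.04.

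**Step 3: check on counts.** Overdispersed counts were simulated with 20 per arm, blocked randomisation within eight strata and a rate ratio of 0.7 in one arm. They were analysed by Poisson regression with a Pearson scale, 600 replicates per setting. SEs are for the log rate ratio.

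| Log-coefficient of the factors | Mean model SE, omitted / adjusted | Empirical SD of the estimate, omitted / adjusted |
|---|---|---|
| 0.1 | 0.268 / 0.264 (2% larger) | 0.268 / 0.269 |
| 0.2 | 0.274 / 0.264 (4% larger) | 0.277 / 0.277 |
| 0.4 | 0.301 / 0.264 (14% larger) | 0.294 / 0.276 (7% larger) |

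The true spread of the estimate changes less than the reported SE, because stratification has already done part of the work. An empirical SD from 600 replicates has a relative error of about 1/√1200 = 2.9%. The adjusted model SE lies 2% to 5% below its own empirical SD, so part of the gap between the model SEs is not a real gain.

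**Step 4: cost of the BMI interaction.** With mean-centred BMI and assumed BMI mean/SD of 32/5, 35/7 or 38/8, adding the interaction raises the SE of the treatment effect by about 1% over a model with BMI as a main effect. The case for a separate model is therefore clarity of meaning more than precision.

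**Step 5: the time-by-treatment terms.** If baseline is only a covariate, T1 and T2 are the only outcome times. Each arm contrast then has one time-by-treatment term, which is the change in effect from T1 to T2. If T0 is itself an outcome and the reference time, there are two such terms per contrast, and they are the effects at T1 and at T2.

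**The case against.** **Stronger readings that a reader might infer.** Three are tempting, and the document supports none of them.

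- *The treatment coefficient's SE is inflated five-fold or more.* With uncentred BMI, the coefficient refers to BMI 0 and its SE is 5.3 to 7.1 times larger under the assumed BMI distributions. That requires BMI to be left uncentred and that coefficient to be reported as the treatment effect. The article says neither, and centring is a detail that may be left to an analysis plan.
- *The primary rate ratio loses its meaning.* The interaction sentence follows the one on secondary analyses, and its purpose is effect modification. The Poisson model is described separately with no BMI term, so on the natural reading its rate ratio is an overall effect.
- *The named primary parameters are the wrong quantity.* Mention of both post-baseline timepoints fits a longitudinal model with T0 as an outcome, where those terms are the effects wanted. The text is ambiguous, not wrong.

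**The case against acting.** The gain is small and rests on an R² that the article does not give. Below about 0.04, adjustment costs slightly more than it returns. With weak or moderate factors the simulation showed no loss in the true spread of the estimate. This is a feasibility trial without a power calculation, and an unseen analysis plan may list the covariates.

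Most of this stands, and it sets the priority. It does not remove the mismatch: the article itself states the adjustment for both models, and that statement leaves out the factors on which it says it stratifies.

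**Conclusion.** The point holds in a limited form. Age and gender are stratified on but appear in no stated model, and BMI appears only in an interaction that belongs, by sentence order, to the secondary mixed model. Intervals for the rate ratios and effect sizes will tend to be somewhat too wide for the design: about 1% to 5% in SE for an assumed R² of 0.02 to 0.10 beyond baseline. Net of three degrees of freedom, there is little or no gain at the low end and about 3% at the high end. The difference is larger only if the factors are strongly prognostic. R², the overdispersion, the prognostic strengths and the BMI distribution are all assumptions.

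The overall effect in the secondary analyses should also come from a model without the BMI interaction. No error rate or decision rule depends on any of this. Low priority, but cheap to put right.

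**What to change.** Replace the adjustment wording in Data analysis with text to this effect: the primary Poisson model and the secondary models adjust for the baseline outcome and for age, gender and BMI as main effects, with age and BMI continuous; the overall treatment effect is taken from these models; a BMI-by-treatment interaction is fitted in a separate exploratory model; treatment contrasts between arms are reported at T1 and at T2. Add that these contrasts are the time-by-treatment terms only if T0 is modelled as an outcome.

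The cost is a few sentences and three degrees of freedom with about 80 participants. The recruitment target stays at 88, and randomisation is untouched. BMI is already derived from self-reported weight and height, and age and gender must be known in order to stratify. If the three factors turn out to be weakly prognostic, adjustment may return nothing or cost about 1% in SE.

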### Study design

TANDEM is a randomized single-blind sham-controlled feasibility trial with four parallel arms: [ABMT + real tDCS], [ABMT + sham tDCS], [ABMT only], and 8-week wait-list control. After baseline assessment (T0), participants will be randomly allocated to a study group. Those allocated to treatment groups will then complete 10 sessions of their allocated treatment over 2 weeks. Outcome measures will be completed first at baseline (T0), then again immediately after completing treatment or after 2-weeks waiting (T1), and finally 6-weeks after completing treatment, or after 8-weeks of waiting (T2). Process outcomes will also be assessed at each treatment session.

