### Intervention

Participants will complete 10 sessions of tele-supervised treatment over 2–3 weeks (i.e., week daily sessions until 10 sessions have been completed). Sessions will involve either concurrent ABMT and real/sham tDCS, or ABMT only. Participants in the waiting control arm will receive ABMT after completion of the T2 assessment.

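### The T1 binge-eating contrast is ranked as primary alongside T2, although 25–50% of its monthly count window falls before treatment and the endpoint is defined as T0 to T2 only

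*Protocol article*

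**What the plan says.** **Outcome.** Primary outcomes: "The primary clinical outcome will be monthly episodes of binge eating, as measured by the Eating Disorders Examination Questionnaire". The same sentence spells this out as "change in the number of monthly episodes of binge eating from baseline (T0) to follow-up (T2"). Study aims agrees: "The primary clinical endpoint will be the change in monthly episodes of binge eating from baseline to follow-up".

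**Collection.** Questionnaires measures: "Participants will complete a battery of questionnaire measures at each assessment (T0, T1 and T2"). Table 1 marks the EDE-Q at all three visits. The article gives no shorter recall period for T1.

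**Timing.** Study design places the second assessment as follows: "then again immediately after completing treatment or after 2-weeks waiting (T1"). It has treated participants "complete 10 sessions of their allocated treatment over 2 weeks". The Intervention section says: "Participants will complete 10 sessions of tele-supervised treatment over 2–3 weeks", and Trial procedure also gives 2–3 weeks. T2 is 6 weeks after treatment ends, or after 8 weeks of waiting.

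**Analysis.** Data analysis names a baseline-adjusted Poisson regression as the primary analysis. It then describes mixed models, labelled secondary, for the primary and secondary outcomes together. Later in the same paragraph comes "Primary parameters will be time vs. treatment interactions at both timepoints after baseline".

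**Intended use.** The Discussion says the 6-week follow-up will show whether effects seen straight after treatment are maintained, and will leave room for slower changes to appear.

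**The concern.** A count that covers a month but is taken only 2–3 weeks after baseline must include days before treatment began, and the T0 count has already covered those days. Treatment cannot alter them, so they pull the T1 rate ratio towards 1 by an amount that the calendar sets. Baseline adjustment does not remove this, because the pre-treatment days are part of the outcome itself.

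Three things are at stake.

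- A diluted estimate carries the same primary rank as the clean T2 estimate, against the endpoint definition elsewhere in the article.
- T1 and T2 estimate different quantities, so comparing them does not answer the maintenance question.
- The overlap is fixed in the waitlist but can be shorter in treated participants, so waitlist contrasts at T1 may also pick up a spurious difference.

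**Working it through.** The plan gives no figure for this overlap, so there is none to reproduce.

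**Inputs from the article.** Days from start to T1: t = 14 (2 weeks; always so in the waitlist) up to t = 21 (3 weeks, treated arms). T2 is 42 days after treatment ends, or day 56 of waiting.

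**Assumptions.** The article says only that the count is monthly. I take a window of W = 28 days, with W = 30 as sensitivity. Treatment starts on the day of T0, the effect is immediate and constant, and the comparison arm stays at its baseline rate.

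**Step 1. Share of the T1 window before treatment:** f = (W − t)/W.

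| W | t = 14 | t = 21 |
|---|---|---|
| 28 | 14/28 = 50% | 7/28 = 25% |
| 30 | 16/30 = 53% | 9/30 = 30% |

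Any gap between T0 and the first session raises the share.

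**Step 2. Rate ratio seen at T1:** RR_obs = f + (1 − f) × RR, with W = 28.

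| True RR | t = 14 | t = 21 |
|---|---|---|
| 0.50 | 0.5 + 0.5 × 0.50 = 0.75 | 0.25 + 0.75 × 0.50 = 0.625 |
| 0.70 | 0.5 + 0.5 × 0.70 = 0.85 | 0.25 + 0.75 × 0.70 = 0.775 |

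For a true RR of 0.50, the log rate ratio keeps ln 0.75/ln 0.50 = 42% of its size at 14 days and ln 0.625/ln 0.50 = 68% at 21 days.

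If the rate instead falls linearly to 0.50 over 14 days of treatment, the T1 count reads 0.5 + 0.5 × (1 + 0.50)/2 = 0.875. That is further from the end-of-treatment rate, so the immediate-effect assumption does not exaggerate the problem.

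**Step 3. T2.** In treated arms the window opens 42 − 28 = 14 days after treatment ends (12 days if W = 30). In the waitlist it opens on day 56 − 28 = 28 (day 26 if W = 30). Neither overlaps the T0 window. A constant RR of 0.50 would therefore read 0.625–0.75 at T1 and 0.50 at T2.

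**Step 4. Waitlist contrast with no treatment effect.** Suppose every arm falls at once to a common fraction c of its baseline rate. The waitlist reads 0.5 + 0.5c. A treated arm in which everyone takes 21 days reads 0.25 + 0.75c.

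- c = 0.70: 0.775/0.85 = 0.91.
- c = 0.80: 0.85/0.90 = 0.94.
- c = 0.70, but all treated in 17.5 days: f = 10.5/28 = 0.375, and (0.375 + 0.625 × 0.70)/0.85 = 0.8125/0.85 = 0.96.
- All treated in 14 days: no spurious difference.

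The values of c are illustrative; the article gives none.

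**The case against.** The strongest reply is that nothing decisive rests on T1. The endpoint is T0 to T2, P-values are declared exploratory, and the trial is sized for feasibility rather than between-group differences. The sentence on primary parameters can also be read as a general statement about the mixed models, which are labelled secondary. It cannot hold literally for every outcome, since Table 1 shows four tasks with no T2 measurement.

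Much of this stands, and it limits the severity. It does not remove the point. The mixed models cover the primary outcome too, so the T1 interaction for binge episodes would still be estimated and called primary. Effect sizes and rate ratios are what this trial sets out to report, so exploratory P-values do not excuse a biased estimate.

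A reader might infer more than the article supports:

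- *That the primary result or the sizing of a later trial is compromised.* It is not. Study aims and Primary outcomes tie the sizing rate ratio to baseline-to-follow-up, where there is no overlap.
- *That half the T1 window always predates treatment.* That holds for 2-week treatment and for the waitlist; at 3 weeks it is a quarter.
- *That any gain from T1 to T2 would be an artefact.* Part of it could be, but a real delayed gain is possible and the authors allow for one.
- *That unequal overlap distorts every comparison.* The three treatment arms share one T1 schedule, so among them the schedule produces dilution only.

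**Conclusion.** The point holds with limited scope. The article ranks the T1 and T2 interactions equally as primary parameters, while its own endpoint definition names T2 only. The T1 contrast for binge episodes is diluted by construction.

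Under the stated assumptions the pre-treatment share is 25–50% (30–53% with a 30-day window), and true rate ratios of 0.50 and 0.70 read 0.625–0.75 and 0.775–0.85. The exact values depend on the window, the onset of effect and the start date. The direction does not, provided the T1 count covers a month. The change from T1 to T2 therefore cannot be read as maintenance or gradual improvement.

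The 0.91 figure is a worst case for waitlist contrasts: every treated participant takes 3 weeks and all arms fall to 0.70 of baseline.

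**What to change.** 1. Amend Data analysis so that the treatment contrast at T2 is the only primary parameter for binge episodes, consistent with Study aims and Primary outcomes.
2. Report T1 monthly counts descriptively by arm, with the overlap stated. Do not use them to estimate the post-treatment effect or maintenance from T1 to T2.
3. Optionally, as a supportive analysis among the three treatment arms only, model the binge counts from the session check-ins from session 2 onward, with log days since the previous session as offset. Session 1 has no previous session and so no defined window, and episodes after the session 10 check-in are not captured.
4. Reconcile the treatment period in Study design with that in Intervention and Trial procedure, since it sets the size of the overlap.

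The cost is a few sentences and no new data. Changing the T1 recall period would have come too late: Trial progress says recruitment ended in February 2022, with data collection to finish by June 2022. The price is that no clean T1 contrast with the waitlist remains, because that arm has no sessions and hence no check-in counts.
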